2.) To examine the role of potential moderators and mediators on intervention effectiveness. Exploratory Aim 2a. To evaluate factors that mediate or moderate effectiveness at 6 and 12 months for all enrolled patients. Potential mediating and moderating variables include patient-level (diabetes distress and self-efficacy and sociodemographics) and facility-level (availability of mental health services) factors. Exploratory Aim 2b. To evaluate factors that mediate or moderate effectiveness at 6 and 12 months for patients in the HOPE arm. Factors include adherence (e.g., session attendance), fidelity (ratings of coach effectiveness), and treatment implementation (e.g., goal-setting quality and self-management behaviors).

3.) Evaluate the potential for embedding HOPE in VA primary care settings, using the RE-AIM framework for evaluating effectiveness of behavioral interventions. Exploratory Aim 3a - Reach. Compare clinical and demographic characteristics of participants with those of all potentially eligible patients. Exploratory Aim 3b - Adoption. Qualitatively elicit PACT clinician and participant perceptions of HOPE to prepare for implementation next steps.

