training workshop, after feedback with study staff (~6mos post-workshop), at exit from the study. Coaches also complete 2 surveys about experience with each veteran (Sect. S, WAI-C and CEC-C) to be administered ~4 mos. after assignment. Survey responses will be entered into a fillable form on a password protected M: drive folder accessible to study staff and coaches (a separate folder from that which contains ID-name link). No PHI or sensitive data will be entered. Once complete, surveys will be entered by staff into a database on the M drive for analysis. Identifying Patient Participants: The study sample will be identified and enrolled using a multi-step screening process. An initial pool of eligible patients with diabetes will first be identified by VISN 16 Data Warehouse and randomly assigned as potential participant lists stratified by clinical site. Information/PHI to be used in this initial data pull that may identify a subject include name, address, phone #, year of diabetes dx and the dates/values of most recent A1c. This info will be used to determine poor glycemic control as an inclusion criterion and to contact the subject to complete the next steps in the screening process. Birth date, race, ethnicity, and gender will also be collected in the initial data pull as descriptive statistics to determine if there are statistically significant differences between interested and not interested patients. The location of the patient's PC facility and their doctor's name will be collected in the initial data pull to identify subjects to guide randomization and coach pairing after randomization respectively. A waiver of informed consent/HIPAA authorization has been approved by the IRB on 2/15/2012 for this initial step of the screening process (Sect S). We will take all measures necessary to ensure the confidentiality/anonymity of all participants. Patients who meet criteria for uncontrolled diabetes and geographic location will receive an opt-out letter about the study. Patients who do not opt out will be contacted by study personnel for the second step of the multi-step screening process. Study RAs will then use a structured, phone-based screening interview to identify patients who preliminarily meet our depression inclusion criteria on the abbreviated PHQ-8 scale. The screening interview will also exclude from that group who screens positive on the PHQ-8 but for whom a phone-based intervention would be inappropriate. Specific procedures and measures to be administered can be found in HOPEIIR Screening Procedures (Sect S). After completing the detailed screening, patients who still meet eligibility will be approached for informed consent and a baseline assessment. The PHQ-9, as part of the baseline assessment, will serve as the final eligibility check in this multi-step screening procedure. Following the phone screening, interested and preliminarily eligible patients will be mailed a copy of the ICF w/out signature lines, along with the baseline measures. After the patient has time to review these docs, study staff will call the patient on the phone to go over the informed consent process. The patient will have the opportunity to ask questions and must demonstrate an understanding of the risks and benefits of participation before verbal consent to participate is achieved. After consent, the subject will begin the baseline assessment. Because this intervention will be used in the medical care of participants, subject's participation in this protocol will result in their medical records being flagged. The following Title 38 U.S.C. 7332 protected information will be collected for scientific research purposes as part of this research protocol: drug and/or alcohol abuse. This info will be maintained in accordance with the security requirements of 38 CFR Section 1.466, or more stringent requirements. This info will not be re-disclosed except back to the VA. This info will not identify any individual patient or research subject in any report of the research, or otherwise disclose patient or research subject identities. The purpose of collecting alcohol and or drug abuse and treatment info (38USC7332) is to conduct scientific research. No personnel involved, in this study, will identify, directly or indirectly, any individual patient or subject in any report of such research or otherwise disclose patient or subject identities in any manner. Baseline Assessment: Subjects who meet eligibility criteria during the phone screening procedures and give verbal consent will participate in a baseline assessment. All assessments (baseline/ 6- /12-month f/u) will be completed by a blinded independent evaluator (IE) over the phone. Baselines will begin with a socio-demographic survey, followed by the PHQ-9 and a myriad of other measures (see HOPEIIR Baseline and Follow Up Measures document in Sect S). A1c collection will be coordinated by IEs. Lab collection is feasible, with high completion rates in our prior VA studies. In EPIC, A1c collection was higher than survey collection rates. All participants who do not meet the final A1c eligibility criteria but were identified as having significant depressive symptoms will be notified of their results, and a note will be placed in their medical record indicating this finding to their PCP. Enrolled participants will also have a note placed in their medical record indicating the presence of clinically significant depressive symptoms and the results of their most recent A1c labs. The participant will be provided with materials on diabetes and depression, and the participant and PCP will be given evidence-based recs for treatment of the depressive symptoms. After baseline, participants will receive \$30. Measures will be repeated from the baseline assessment at 6 and 12-mos., but no demographics. If staff cannot reach a veteran 3x by phone to schedule f/up, a letter may be sent. Packets will be mailed to participants as a courtesy for each assessment so that they may follow along with the measures as they are administered by phone (Sect S). Randomization: All consented participants who complete the baseline and are eligible after baseline and blood draw will be randomized to HOPE or Enhanced Usual Care. Eligible participants at each site will be randomly assigned by a RA following the baseline evaluation. In accordance with VA policy and procedures, participants randomized to the HOPE intervention will receive VHA Form 10-3203 (Sect S) with

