
clinicians based on response categories. Evaluating the potential for embedding the HOPE intervention within VA (Assessing Implementation): Exploration of reach--We will compare the demographic and clinical characteristics of study participants from the study sites to those of potentially eligible patients typically cared for at each CBOC and the MEDVAMC. For each site, we will test whether patients who participated differed from (a) patients who were approached but refused enrollment and (b) all remaining patients who would have met inclusion criteria but who were not included in the study, using analysis of variance for continuous variables and chi-square tests for categorical variables. The variables of interest will include age, gender, race, BMI, Deyo comorbidity score, and presence of PTSD or major depression. These variables will be obtained from the VISN 16 data warehouse. The potentially eligible patients cared for at each facility will be determined using diagnoses of diabetes and depression from the inpatient and outpatient files and A1c values from the VISN 16 data warehouse (with IRB approval). Exploration of adoption--We will evaluate the perceptions and practices of clinicians regarding intervention processes including the incorporation of behavioral goals and action plans within the progress notes and treatment plans described by PCPs. To accomplish this aim, we will purposively sample PCPs at each clinical site, including those who have cared for control and intervention subjects. We will use respondents' PACIC scores to purposively sample low and highly rated PCPs on the patient engagement and goal-setting subscales. Recruited PCPs will be evaluated using in-depth interviews to elicit their perceptions of the overall intervention procedures and their use of any constituent elements of each intervention. Consistent with established qualitative interview methodology, interviews will be audiotaped, transcribed, and analyzed using a deductive approach based on a coding system developed from our interview guide. Coded units will be reexamined for relationships and clustered into patterns. Based on past experience, we anticipate that each interview will last 30 minutes. Quantitative analyses will also be done on the coach surveys completed pre-, post-, and 6-months-post-training to assess change over time. The results of these quantitative and qualitative analyses will guide future implementation studies of the HOPE intervention in usual VA care.

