## Section J: Consent Procedures

### J1. Waiver of Consent

Will any portion of this research require a waiver of consent and authorization?

Yes

Please describe the portion of the research for which a waiver is required. (Example: chart review to determine subject eligibility)

A waiver of consent and authorization is required in order to conduct chart reviews to identify potentially eligible participants for the study. Once identified, subjects will be mailed an opt out letter. \* Please note that the study is no longer recruiting participants \*

Explain why the research and the use or disclosure of protected health information involves no more than minimal risk (including privacy risks) to the individuals.

The waiver is being requested to only identify potentially eligible Veterans. Veterans will be mailed an opt-out letter and be given the opportunity to call in to decline participation. Veterans that don't opt out, will be contacted for a screening call and will be explained that participation is strictly voluntary. After confirmation at the screening call, Veterans will be scheduled for a baseline assessment. At the assessment a complete description of the study will be provided and Veterans will have the option to decline before study related data is collected. Any data collected before the baseline assessment will not be used from Veterans that declined participation.

Explain why the waiver will not adversely affect the privacy rights and the welfare of the research subjects.

A waiver of the informed consent requirement for recruitment purposes will not adversely affect the rights or welfare of Veteran participants. The waiver is only being requested to conduct chart reviews to exclude Veterans not eligible for the study. Veterans that are not excluded will be mailed an opt out letter. At the time of the screening call Veteran's will be explained the study and that participation is completely voluntary and their decision to participate or not will not affect the service-related right to which they may be entitled. Additionally, at the scheduled baseline study staff will review the detailed information document providing another opportunity for Veteran participants to decline participation.

Explain why the research could not practicably be conducted without the waiver and could not practicably be conducted without access to and use of the protected health information.

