Clinicians will self-identify from presentations by study staff in primary care clinics. Study staff will arrange a private meeting with interested clinicians, where they will review and sign the 10-1086 together. This may be done immediately after the presentation or at a later date, depending on clinician availability and preference. The clinicians will have a chance to hear all the details of the study and ask questions, and will be provided with a copy of the signed ICF. We will use the VISN 16 data warehouse to identify potentially eligible patients by these steps: 1. Identify patients with a PCP visit during the past year at the VAMC and/or the CBOCs. 2. Search for patients with type 2 diabetes by ICD-9 codes. A standardized medical record review will confirm diabetes (DM) dx and evidence of exclusion criteria. 3. After verification, patients will be contacted for initial recruitment via a mailed opt-out letter. Letters, written at a 6th grade reading level, will indicate that research personnel will contact the patient after 4 days unless the patient calls the given 800# to opt-out, as directed by the letter. 4. After waiting, a delegated researcher will contact patients to administer a screening protocol. Those who still meet criteria will be mailed a baseline packet and an ICF w/out signature lines. A delegated IE will then call to review the documents and collect verbal consent. Patients who pass the initial screening and consent to participate but are subsequently excluded by the baseline inclusion criterion (PHQ9 or A1c) may be re-contacted at a later date. If interested, the patients will be re-assessed with the PHQ-9 and/or A1c measure to see if they have become eligible for randomization. A waiver of consent will be requested to initiate the medical record review using the VISN 16 data warehouse. Specifications for the waiver are: a) Explain why the use or disclosure of PHI involves no more than minimal risk to the individuals and that the waiver will not adversely affect the privacy rights and the welfare of the individuals. The waiver of consent will only be used to identify a) dx of DM; b) level of DM control; and c) telephone contact info. We will use this info to identify potentially eligible patients and approach them for informed consent. Patients will be sent an opt-out letter prior to any phone contact. For those patients who opt out using the 800#, all PHI will be erased from our files. Patients who do not opt out, will be given the option to provide verbal consent after the waiting period. Those patients who refuse verbal consent will also have their PHI erased from our files. b) Explain why the research could not practicably be conducted w/out the waiver and could not practicably be conducted w/out access to and use of the PHI. Initial access to the PHI is necessary to identify potentially eligible patients. Given our strict eligibility criteria, it would be impossible to recruit our targeted sample of patients w/out first limiting recruitment to uncontrolled diabetics who could then be approached to evaluate for depressive symptoms. These patients rarely enroll in studies w/out first being screened and identified as potential candidates for enrollment. The telephone nature of our screening and intervention procedures requires that we first identify a large sample of potentially eligible patients. Given these circumstances and criteria, our recruitment would be virtually impossible w/out first limiting enrollment to those with known DM with poor A1c control. This can only be done with an initial waiver of consent for the screening criteria. c) Will additional pertinent info be provided to subjects after participation? Yes, Subjects will be provided with feedback on the info collected during the study. They may also request the results of their lab work. Study subjects will receive personalized info regarding their diabetes and depression management, according to the intervention modules.

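### Exploratory Aim 3a (Reach): the planned comparison with refusers conflicts with the commitments to erase or not use decliners' data, and the diagnosis-based eligible pool partly builds in the comparison on major depression

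*Protocol*

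**What the plan says.** Exploratory Aim 3a (Protocol, Section D) is to "Compare clinical and demographic characteristics of participants with those of all potentially eligible patients". G2, under exploration of reach, turns this into two site-level comparisons. In comparison (a), participants are tested against "patients who were approached but refused enrollment". In comparison (b), the other group is "all remaining patients who would have met inclusion criteria but who were not included in the study". The variables are age, gender, race, BMI, Deyo score, and PTSD or major depression, all taken from the VISN 16 data warehouse.

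F2 adds a related test. Birth date, race, ethnicity and gender from the initial data pull are collected "to determine if there are statistically significant differences between interested and not interested patients".

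Section J says something different about the same people:
- J1: "Any data collected before the baseline assessment will not be used from Veterans that declined participation".
- Recruitment and waiver text after J1a, on opt-outs: "For those patients who opt out using the 800#, all PHI will be erased from our files".
- Same text, on refusers: "Those patients who refuse verbal consent will also have their PHI erased from our files".

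On how the eligible pool is found, G2 says: "The potentially eligible patients cared for at each facility will be determined using diagnoses of diabetes and depression from the inpatient and outpatient files", together with A1c values. The inclusion criteria in F1 instead rest on a self-reported PHQ-9 score of at least 10 and ask for no depression diagnosis.

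**The concern.** There are two separate problems.

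The first is a contradiction about data. Comparison (a) and the F2 test need individual characteristics of people who declined, and a record that they declined. Section J commits the study to erasing identifiable data on two groups of decliners and to not using what was collected on decliners before baseline. The analyst has no consistent instruction on whether the comparison may be done or with what data.

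The second is a mismatch of definitions. Group (b) is described as patients who would have met the inclusion criteria, but it is found by a different depression criterion from the one participants met. A characteristic close to that criterion, major depression, is then tested between the groups.

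At stake is what the trial can say about whom the intervention reached. G2 says the implementation analyses will guide later implementation studies, so an artefact here could be carried forward.

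**Working it through.** The Reach analysis states no sample size, power or significance level, so there is no figure to reproduce. The check is a comparison of texts, plus one illustration.

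**1. Refusers, by the point at which they leave**

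| Point of refusal | Section J commitment | Needed by G2 (a) and F2 |
|---|---|---|
| Opts out by telephone after the letter | Identifiable data erased | Characteristics, and the fact of refusal |
| Declines at the screening call | Pre-baseline data not used (J1) | Same |
| Refuses verbal consent | Identifiable data erased; pre-baseline data not used | Same |

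At none of these points do the two columns agree. For a refusal at the screening call the conflict rests on the non-use sentence in J1, because the erasure sentences name only opt-outs and refusers of verbal consent.

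**2. Does a new warehouse extract solve it?** The warehouse supplies covariates. The protocol nowhere says that it records who refused this study. The data items F2 lists for the initial pull do not include BMI, Deyo score, PTSD or major depression, so G2 would have to link refusers back to the warehouse by identity. Once identity is erased that link is gone. Refusers who carry the diabetes and depression codes and a qualifying A1c would come back unmarked inside group (b).

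**3. Pool against eligibility.** Participants: PHQ-9 of 10 or more, diagnosis not required. Pool: depression diagnosis on file, PHQ-9 not used. The pool therefore leaves out symptomatic patients without a diagnosis and admits diagnosed patients below the threshold. Every pool member has some depression diagnosis by construction and participants need have none, so a difference in major depression can arise without any selective enrolment.

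**4. Illustration of how far the definitions can diverge**
- p = 1/3, the share of diabetic patients with clinically significant symptoms. Section C says almost one third; using it for PHQ-9 of 10 or more is an approximation.
- s = probability of a depression code given PHQ-9 of 10 or more; assumed 0.3 to 0.7.
- f = probability of a code given PHQ-9 below 10; assumed 0.05 to 0.20.
- Pool share = s·p + f·(1 − p). Share of the pool at or above threshold = s·p / pool share. Share of symptomatic patients missed = 1 − s.

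| s | f | Pool per 1,000 diabetic patients | Pool with PHQ-9 ≥ 10 | Symptomatic patients missed |
|---|---|---|---|---|
| 0.3 | 0.05 | 133 | 75% | 70% |
| 0.3 | 0.20 | 233 | 43% | 70% |
| 0.7 | 0.05 | 267 | 88% | 30% |
| 0.7 | 0.20 | 367 | 64% | 30% |

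Worked case, s = 0.3 and f = 0.20: 0.3 × 1/3 + 0.20 × 2/3 = 0.100 + 0.133 = 0.233; 0.100 / 0.233 = 43%. By PHQ-9 alone the pool would be about 333 per 1,000. The protocol gives neither s nor f, so the table shows only that the two definitions can select clearly different groups. It does not estimate the gap in this trial.

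**The case against.** The strongest case on the other side has four parts.

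*The aim survives.* A reader might infer that Aim 3a cannot be answered at all. The text does not support that. The aim in Section D asks for participants against all potentially eligible patients; refusers are a comparator added in G2. The warehouse comparison can be run as a proxy, and age, gender, race, BMI and Deyo score are not criteria used to form the pool. This stands.

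*Neither an absence of refuser data nor a breach is shown.* A reader might infer that no refuser record can exist, or that running comparison (a) would breach the waiver. The erasure sentences concern identifiable data in the study's files and do not say that de-identified or aggregate data are destroyed. F2 reports IRB approval of a waiver for the initial pull and lists the interested/not-interested comparison among the uses of that pull. G2 refers to IRB approval for its warehouse data. The approved waiver itself is not in the document. This also stands: what can be shown is inconsistent wording. It does not remove the inconsistency, since J1 bars use of any pre-baseline data from decliners and no provision for a de-identified refuser file appears.

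*A proxy is unavoidable.* No PHQ scores are described for unscreened patients, so some substitute is needed. That is fair. It argues for naming the substitute, not for describing the group as meeting the inclusion criteria.

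*Defining the pool before any depression criterion is no clear improvement.* On the Section C figure, about two thirds of such a pool (1 − 1/3) would lack clinically significant symptoms, while every participant has PHQ-9 of 10 or more. That exchanges one selection artefact for another, so it is not recommended here.

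**Conclusion.** The point holds in limited form. Comparison (a) and the interested/not-interested test cannot be carried out consistently with Section J as written, and a fresh warehouse extract does not cure this because nothing stated would still mark who refused. Group (b) is a diagnosis-based proxy, not the set of patients who would have met the inclusion criteria, and its comparison with participants on major depression is partly built in.

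The size of that built-in difference cannot be derived. A reader might try: if 40% to 70% of participants carried a depression code against 100% of the pool, the gap would be 30 to 60 percentage points (100 − 70 and 100 − 40). The document does not support that figure. The 40% to 70% has no source in it, and the calculation concerns any depression code, whereas G2 compares major depression.

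The conclusion rests on the protocol alone, without the approved waiver or knowledge of which records exist. Aim 3a is exploratory, so the HbA1c and PHQ-9 analyses are unaffected.

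**What to change.** - **Refusers.** Reconcile F2, G2, J1 and the recruitment text of Section J. State which de-identified or aggregate data on refusers, if any, the approved waiver allows to be kept and used, and for which points of refusal. If none exist, drop comparison (a) and the interested/not-interested test and report both as not done.
- **Eligible pool.** In G2, label group (b) a diagnosis-based proxy for potentially eligible patients. Keep the planned comparisons on age, gender, race, BMI and Deyo score with that label. Report depression diagnosis descriptively in each group, without a significance test, and say that it overlaps the way the pool was selected.

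The cost is protocol wording and a check of the waiver and of the records held. J1 notes that recruitment has ended, so a change to what is retained may come too late. In that case comparison (a) is lost, and the report should say so. No new data collection and no change to the primary analyses is needed.

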**Section F: Design/Procedure****F1. Design**

Select one category that most adequately describes your research:

z.r) Randomized, Efficacy Study -- Surgical Techniques/Interventions

Discuss the research design including but not limited to such issues as: probability of group assignment, potential for subject to be randomized to placebo group, use of control subjects, etc.

We propose a randomized clinical trial to compare the effectiveness of HOPE with that of enhanced usual primary care (EUC) for distance-based Veterans with comorbid diabetes and depressive symptoms receiving

primary care services at the VA. Randomization will occur at the patient level and be stratified by clinical site. In addition, we will evaluate the durability of the treatment over a 6-month period following the active-treatment phase. To better understand the mechanics of change, we will conduct an exploratory examination of the mediating and moderating variables associated with changes in the primary outcomes (HbA1c levels, depression symptoms) at both 6 and 12 months. Additional exploratory analyses will attempt to better understand the relative strengths, weakness, barriers, and facilitators important to future implementation if the intervention produces significant changes.

The proposed study will enroll 242 patients with diabetes and depressive symptoms who receive care in VA CBOCs throughout Southeast Texas, as well as MEDVAMC patients living >20 miles from the hospital who face similar distance related treatment barriers. 60% of the participants (n=146) will be randomized to receive 9 behavioral coaching sessions in 6 months (active intervention), followed by 6 months without coaching (maintenance period); the other 40% (n=96) will receive EUC, which will include the provision of educational materials and feedback about diabetes and depression. All consented participants (both treatment arms) and their PCPs will be notified of the diabetes control and depressive symptoms and provided with guideline-based recommendations for treatment of depressive symptoms. Randomization will be stratified by clinical site.

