#### Exclusion Criteria:

We will exclude potential participants only for clinical factors that would render a telephone-based behavioral activation intervention inappropriate. Specific exclusion criteria are: (a) lack of regular access to a telephone; (b) significant cognitive impairment (three or more errors) on an established six-item screening exam; and (c) meeting criteria for bipolar, psychotic, or substance-abuse disorders; (d) presence of hearing impairment; (e) their medical chart recommends not titrating therapy due to prior history of significant hypoglycemic events; or (f) they live within 20 miles of the MEDVAMC. Patients will be secondarily excluded if their HbA1C level falls below 7.5% at baseline assessment, or if they report suicidal ideation on the PHQ-9 at baseline assessment.

Patients receiving mental health services for conditions other than bipolar, psychotic or substance-abuse disorders at the time of study recruitment will not be excluded. All mental health treatments and health service-use characteristics will be included in study analyses as covariates.

Coaches do not have any exclusion criteria. All disciplines in primary care are invited to participate.

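### As written, Reach comparison group (b) takes in patients the trial could not enrol: those living within 20 miles of the MEDVAMC and those with excluded psychiatric or substance-abuse diagnoses

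*Protocol*

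**What the plan says.** Section D, exploratory Aim 3a, compares participants with all potentially eligible patients. Section G2 (exploration of reach) makes this operational for each CBOC and the MEDVAMC. On the pool it says: "The potentially eligible patients cared for at each facility will be determined using diagnoses of diabetes and depression from the inpatient and outpatient files". The same sentence adds A1c results taken from the regional warehouse, under IRB approval.

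Participants are then tested, site by site, against two groups. Group (a) is those who were invited and declined. Group (b) is described as "all remaining patients who would have met inclusion criteria but who were not included in the study". The variables are age, gender, race, BMI, Deyo comorbidity score, and PTSD or major depression. The reach text mentions no exclusion criterion and no distance limit.

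The rules that matter here are found elsewhere. The exclusion criteria remove patients if "they live within 20 miles of the MEDVAMC" and those "meeting criteria for bipolar, psychotic, or substance-abuse disorders". The design text in F1 describes the sample as CBOC patients, "as well as MEDVAMC patients living >20 miles from the hospital who face similar distance related treatment barriers". Neither rule is among the patient inclusion criteria, which are a diabetes diagnosis, an average HbA1c above 7.5% in the prior 12 months, and clinically significant depressive symptoms.

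**The concern.** A reach analysis is useful only if the comparison group could have been reached. Participants pass a location filter and a chart review for excluded diagnoses before anyone contacts them, whereas group (b) as defined passes neither. A difference between the two then mixes two things: who among the enrollable patients took part, and who was ruled out by design. Residence and psychiatric history can plausibly relate to race, age, comorbidity and recorded PTSD or depression, which are among the variables tested. A design restriction could be reported as a failure of reach, or a real imbalance could be offset and missed. Section G2 says these results will guide later implementation studies of HOPE.

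**Working it through.** The protocol gives no figure for the Reach analysis, so there is nothing to reproduce. The check is a comparison of texts.

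| Rule | Applied to participants | Applied to group (b) as written |
|---|---|---|
| Diabetes diagnosis | Yes (inclusion criteria) | Yes (diagnoses in inpatient and outpatient files) |
| A1c | Yes (inclusion criteria, rechecked at baseline) | A1c values named; the threshold comes only through the reference to inclusion criteria |
| Primary care visit in the past year | Yes (Section J, recruitment steps) | Not stated |
| More than 20 miles from the MEDVAMC | Yes (F1 and exclusion (f); F2 filters on location before the opt-out letter) | Not stated; not an inclusion criterion |
| No bipolar, psychotic or substance-abuse disorder | Yes (exclusion (c); J1 describes a problem-list search before contact) | Not stated; not an inclusion criterion |
| No cognitive impairment | Yes (J1 problem-list search, then the six-item screen) | Not stated |

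The text gives a rule for the pool, and a programmer who followed it would remove none of the patients in the last three rows. Group (a) differs: these patients were approached, so they had already passed the location and chart filters.

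**Can the missing rules be applied?** The initial warehouse pull in F2 holds "name, address, phone #, year of diabetes dx and the dates/values of most recent A1c", so distance can be computed. It lists no psychiatric codes, but G2 already plans to draw diagnoses from the inpatient and outpatient files, so exclusion codes can come from the same source.

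**Scale, under assumptions only.** None of the following inputs is in the documents. Suppose participants mirror the eligible MEDVAMC patients exactly. A binary trait has prevalence 25% beyond 20 miles and 35% to 45% within, a gap g of 0.10 to 0.20. A share q of 0.40 to 0.80 of the coded MEDVAMC pool lives within 20 miles.

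- False difference = q × g. Lowest: 0.40 × 0.10 = 0.04. Highest: 0.80 × 0.20 = 0.16.
- Middle case, q = 0.60 and g = 0.20: pool prevalence = 0.25 + 0.12 = 0.37. With 60 participants against 2,000 pool patients, the pooled proportion is (15 + 740)/2,060 = 0.3665. SE under the null = √(0.3665 × 0.6335 × (1/60 + 1/2,000)) = 0.0631. SE under the alternative = √(0.25 × 0.75/60 + 0.37 × 0.63/2,000) = 0.0569. Chance of p < 0.05 = Φ((0.12 − 1.96 × 0.0631)/0.0569) = Φ(−0.07) = 0.47. With 100 participants the same steps give Φ(0.52) = 0.70.
- Over the full range with 60 to 100 participants, the chance is 9% to 92%. With only 20 participants it is about 6% to 28%, but the biased estimate remains.
- Masking, same middle case: if 37% of participants had the trait against 25% of eligible patients, a real 12-point imbalance, the observed difference from the pool would be 0.37 − 0.37 = 0.

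**The case against.** The best defence is that the protocol is silent here and does not waive the exclusions. It calls the pool potentially eligible, which suggests they were meant to apply. The sentence gives no code list, A1c threshold or window, and such extract rules for an exploratory aim are often left to a later specification. This stands in part: the text does not say that no exclusion applies. But it does say how the pool is determined, and it ties group (b) to inclusion criteria, so the literal reading is an incomplete rule that gives a biased contrast.

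Several stronger readings are tempting and are not supported:

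- A reader might infer that Aim 3a as a whole compares participants with patients who could never be enrolled. Group (b) would be a mixture of enrollable and non-enrollable patients, and group (a) is largely free of the problem.
- A reader might take the percentages above as estimates. They depend entirely on assumed prevalences, shares and counts.
- A reader might argue that the study's own notes in the medical record inflate recorded depression among participants. The protocol describes notes to the primary care provider, not coded diagnoses, and does not say when the variable is read. This is speculation.
- A reader might want patients who failed the study's screening removed from the pool. J1 says that information collected on ineligible screened patients will not be used, so that step conflicts with the protocol as it stands.

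The objection on cost has some force. The initial pull holds no psychiatric codes, and Section J limits the recruitment waiver to diabetes diagnosis, diabetes control and telephone contact details. It is mostly answered by G2, which already plans a diagnosis extract under IRB approval.

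**Conclusion.** The concern holds for group (b). Its stated definition omits the distance rule and the excluded diagnoses, both of which were applied to participants before contact. The contrast can therefore attribute the trial's own exclusions to reach, or hide a real difference. The direction and size of the distortion cannot be derived from the documents. They depend on how many coded patients are ineligible at each site and how far those patients differ from eligible ones. The aim is exploratory, so the harm is confined to the interpretation of Reach and what is built on it; the primary comparison and the sample size are unaffected. Identifying depression by diagnosis code when the trial enrols on the PHQ-9 is a separate matter, and correcting it would not remove these patients.

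**What to change.** Amend the reach text in G2 so that group (b) is restricted by every recruitment rule the warehouse can show:

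- the primary care visit in the past year and the A1c entry rule;
- no coded bipolar, psychotic, substance-abuse or cognitive-impairment diagnosis;
- the distance rule. F1 and the exclusion list must first be reconciled: F1 ties the 20-mile limit to MEDVAMC patients, while exclusion (f) applies to anyone living that close, including CBOC patients.

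Read all Reach variables for participants and pool at one common date, that of the initial data pull. List as a limitation the exclusions that the warehouse cannot show: telephone access, the six-item cognitive screen and suicidal ideation on the PHQ-9. Do not remove screening failures unless that step is first reconciled with J1.

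The cost is programming and some diagnosis codes added to an extract already planned under IRB approval; the team should confirm that the approval covers them. No patient contact is needed. The pool will be smaller, and coded exclusions will only approximate the chart review and screening interview.
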